#### Biomedical Outcomes

A blood test and physical examination were only carried out in Spain. A blood test was performed at the beginning and end of the study to measure blood count, creatinine, urea, glucose, glutamic pyruvic transaminase, glutamic oxaloacetic transaminase, gamma-glutamyl transferase, total cholesterol, HDL cholesterol, and triglycerides in all participants. Automated, routine colorimetric methods are used. Non-HDL cholesterol is calculated by subtracting HDL from total cholesterol, and low-density lipoprotein cholesterol is estimated using Friedewald’s formula [39]. HbA_1c_ was measured by High-Performance Liquid Chromatography (using Diabetes Control and Complications Trial standards, following National Glycohaemoglobin Standardisation Programme) in people with T1D only.

As part of the physical examination, the patient’s weight and height were measured to calculate BMI. Measurements of the abdomen, arm, and calf circumference are taken with a non-extensible measuring tape. Grip strength is assessed using a Jamar dynamometer, and a Holtain plicometer (Holtain Ltd) is used to measure the triceps skinfold. Body fat and muscle mass are estimated using a Tanita DC-360 (Tanita) bioimpedance meter. Arm muscle circumference is calculated from the triceps skinfold and arm circumference measurement. Muscle quality is calculated based on the muscle mass from the bioimpedance analysis and the grip strength measurement [40]. Finally, the functional test sit-to-stand with 5 repetitions is performed [41].

For participants with T1D, time in relevant ranges (see above), average glucose, glucose management indicator, and hypoglycemic events are recorded by the app from a CGM FSL 2 or 3 (Abbott). Hypoglycemic events are also recorded or confirmed manually.

#### Perceived Quality of Life

The EQ-5D questionnaire [42] is used to assess health-related quality of life in all participants. It consists of 2 parts: The first part contains 5 health dimensions (mobility, self-care, activities of daily living, pain and discomfort, and anxiety and depression). For each dimension of the EQ-5D, severity levels are coded: 1 if the answer choice is “no (I have) problems,” 2 if the answer choice is “some or moderate problems,” and 3 if the answer choice is “many problems.” The higher the score, the worse the health dimension. The second part of the EQ-5D is a scale from 0 to 100. On this scale, the individual should mark the point that best reflects their assessment of their overall health status, with 0 being the lowest assessment of their health status and 100 being the best.

The Life with Type 1 Diabetes (Vida con Diabetes tipo 1; ViDa1) [43], a questionnaire for health-related quality of life in patients with T1D, is also used for the group of individuals with T1D. The ViDa1 has 34 items that are grouped into 4 different dimensions: interference with life, self-care, well-being, and worry about the disease. It is a questionnaire that can be self-administered with a Likert-type response format in which a total score per subscale is obtained. Interference with life: (items 1-12), self-care (13-23), well-being (24-29), and worry about illness (30-34). Each item is scored from 1 “strongly disagree” to 5 “strongly agree.” For correction, the scores obtained in each subscale are added together. To ensure an accurate interpretation, the scoring for items 12, 23, and 27 must be reversed (a score of 1 indicates strongly agree, while a score of 5 indicates strongly disagree).

#### Knowledge and Attitudes

To measure diabetes self-management behaviors, the Summary of Diabetes Self-Care Activities (SDSCA) is used [44]. It consists of 11 items that address different areas of self-care present in people with diabetes mellitus, such as diet, physical activity, medication, self-testing of capillary glycemia, and smoking. It presents a response scale from 0 to 7, depending on the number of days that the person has carried out a certain behavior in the previous week. The smoking item has a dichotomous response. The questionnaire has no cutoff point, so each item must be assessed individually.

To assess the knowledge acquired about healthy habits, the European Health Literacy Survey is used [45]. The questionnaire consists of 16 questions that classify the degree of difficulty perceived by the participant in each task or situation as: 1 “very easy,” 2 “easy,” 3 “difficult,” 4 “very difficult,” or 5 “don’t know/no answer.”

#### Satisfaction and Feedback

The System Usability scale (SUS) [46] and mHealth App Usability Questionnaire (MAUQ) [47] are used. The SUS scale is a 10-item questionnaire scored on a 5-point Likert-type scale from 1 (strongly disagree) to 5 (strongly agree). The overall score ranges from 0 to 100. A system with a score above 85 is considered to have excellent usability. The MAUQ assesses the ease of use, interface, satisfaction with, and usefulness of mHealth apps for end users. It consists of 18 items, with 7 response options for each item, ranging from 1 “strongly disagree” to 7 “strongly agree.”

Table 1 summarizes the procedures associated with the trial.

**Table 1 table1:** Study schedule.

Months and procedures	Screening	January (Initial visit app download)	February (Initial visit app download)	March	April	May (Final visit)	June (Final visit)
Informed consent	✓	—^a^	—	—	—	—	—
Demographics	✓	—	—	—	—	—	—
Medical history	✓	—	—	—	—	—	—
Physical examination^b^	—	✓	✓	—	—	✓	✓
Blood tests^b^	—	✓	✓	—	—	✓	✓
Body composition^b^	—	✓	✓	—	—	✓	✓
Questionnaires	—	✓	✓	—	—	✓	✓
Usability, engagement, and digital health literacy scales	—	—	—	—	—	✓	✓
Likert scale (primary outcome)	—	—	—	—	—	✓	✓
Data collection (glucose sensor and physical activity device)	—	✓	✓	✓	✓	✓	✓

^a^Not applicable.

^b^Procedures performed only in the Spain center.

### Statistical Analysis

Descriptive results will be presented as mean (SDs), or median (IQRs) for continuous variables, and frequencies and percentages for categorical variables. The primary endpoint is the difference in Likert score between the 2 groups in the self-reported achievement of the individual, self-defined aim at the end of the study. The intervention and control groups will be compared using a Student *t* test (2-tailed) or a Mann-Whitney *U* test. We will also perform linear regression to compare the groups with adjustment for the stratification factor center. For comparison of changes in variables measured at baseline and end of study, we will use linear regression or logistic regression adjusting for the baseline measurement [48]. Logarithmic transformation may be used. A *P* value below .05 will be considered significant.

An intention-to-treat analysis will be performed (including all randomized participants, regardless of their adherence to the intervention).

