### Randomization and Blinding

After registration in the WARIFA app, participants were randomly assigned in a 1:1 ratio by the system, using a computer-generated randomization list. This randomization was stratified by T1D status (yes or no) and center, to ensure balance within each group. The app was downloaded from Google Play, with the same download link for all participants, who were unaware of what exactly to expect from the app. Once downloaded, and after registration, eligibility criteria were confirmed, informed consent was given within the app and participants were randomized: one feature set in the app was available for the control group and another for the intervention group. This procedure was done individually by the participants, avoiding interaction amongst them. Both the researchers and the participants were unaware of group allocation, and the researchers who analyze the data are blinded, too.

In the Norwegian and Romanian centers, the app was downloaded either independently by the participant or with assistance (Norway). In the Spanish center, visits were face-to-face, as blood tests and physical examinations were carried out.

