### Power and Sample Size

The sample size was calculated for the primary outcome (Likert scale from 1 to 10 with a target defined by the participant). A population of people with T1D was used as the reference population, based on a previous study [38,49]. The common SD in the intervention and control groups is assumed to be 2.07 [38]. With a significance level of 0.05 and a power of 0.8 in a 2-sided 2-sample *t* test (2-tailed), 47 subjects are necessary in both groups to detect a statistically significant difference greater than or equal to 1.3 units. Allowing for a potential loss to follow-up of 10%, we estimated a total required sample size of 52 participants in each group. Participants with T1D are only recruited in Spain. All 3 centers aimed to recruit an equal number of participants, that is, 36 participants each (aiming at a total of 108).

The analyses will primarily be performed on the total sample for common outcomes. Regarding the group of participants with T1D, as the study lacks the power to detect clinically relevant changes in T1D-specific clinical outcomes, no definitive conclusions will be drawn from these results. Instead, the results will inform sample size estimation and the design of a subsequent trial targeting the T1D population specifically.

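### T1D status is a randomization stratum but enters no stated model for the primary outcome, so intervals may be somewhat too wide and a little power lost if the strata predict the Likert score

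*Protocol article*

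**What the plan says.** Randomization and Blinding names two stratification factors: "This randomization was stratified by T1D status (yes or no) and center, to ensure balance within each group".

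Statistical Analysis first gives an unadjusted comparison for the primary endpoint: "The intervention and control groups will be compared using a Student *t* test (2-tailed) or a Mann-Whitney *U* test". It then adds: "We will also perform linear regression to compare the groups with adjustment for the stratification factor center". The wording treats center as the only stratification factor. For outcomes measured at baseline and at the end, the models are described as adjusting for the baseline value; no stratum term is mentioned.

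Power and Sample Size adds two relevant facts. The populations are pooled: "The analyses will primarily be performed on the total sample for common outcomes". T1D sits inside one center: "Participants with T1D are only recruited in Spain".

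**The concern.** When randomization is balanced within strata, the treatment estimate varies only with the within-stratum scatter. An analysis that leaves the strata out still counts between-stratum variance as noise, so its standard error is larger than the true sampling variation.

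A center term does not stand in for T1D status if Spain enrolled both populations, because it gives all Spanish participants one common mean. A difference in the primary score between the two Spanish groups is conceivable. Only T1D participants may choose the hypoglycemia goal (Outcomes), and the glucose features exist only for them (Intervention). At stake is precision on the primary comparison in a trial that recruited 88 participants against a target of 108.

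**Working it through.** **Inputs from the article.** SD 2.07, difference 1.3, two-sided alpha 0.05 and power 0.80 (Power and Sample Size). Recruited: Spain 34, Norway 34, Romania 20, total 88; 42 intervention and 46 control (Results).

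**Assumptions.** The T1D count and stratum differences are not given. I take 17 T1D and 17 general participants in Spain, hold the total SD at 2.07 and vary the gap g between the two Spanish groups.

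**The plan's own figure.** n per group = 2(1.960 + 0.842)² × 2.07² / 1.3² = 2 × 7.849 × 4.285 / 1.69 = 39.8, so 40; the exact t calculation gives 40.8, so 41. The article states that "47 subjects are necessary in both groups to detect a statistically significant difference greater than or equal to 1.3 units". The stated inputs do not reproduce 47. That is a separate matter and does not drive this point. With 42 and 46 analyzed, the unadjusted t test has about 83% power for 1.3 units, and about 79% after a 10% loss.

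**Isolating the omission of T1D.** Put Spanish T1D at +g/2, Spanish general at −g/2, and Norway and Romania at 0, so that all center means are equal.

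- Between-stratum variance: B = (34/88)(g/2)².
- Center-only standard error: SE_c = √(2.07² × 4/88) = 0.441, because center explains nothing here. The actual 42/46 split gives 2.07 × √(1/42 + 1/46) = 0.442, essentially the same.
- Standard error with all strata, which is also the true SD of the estimate: SE_s = √((2.07² − B) × 4/88).
- Power, center only: Φ((1.3 − 1.989 × SE_c)/SE_s). Power, all strata: Φ(1.3/SE_s − 1.989).

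| Gap g | B | SE_s | SE_c too large by | Power, center only | Power, all strata | Loss (points) |
|---|---|---|---|---|---|---|
| 0 | 0 | 0.441 | 0% | 83.1% | 83.1% | 0 |
| 0.5 | 0.024 | 0.440 | 0.3% | 83.1% | 83.3% | 0.1 |
| 1 | 0.097 | 0.436 | 1.1% | 83.4% | 83.9% | 0.5 |
| 2 | 0.386 | 0.421 | 4.8% | 84.2% | 86.4% | 2.2 |
| 3 | 0.869 | 0.394 | 12.0% | 85.8% | 90.5% | 4.7 |

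A simulation of permuted-block allocation in the four strata (17/17/34/20; 20,000 runs per gap) agrees. Power for center only versus all strata was 83.4% versus 84.0% at g = 1, 83.7% versus 86.0% at g = 2 and 85.5% versus 90.5% at g = 3. The type I error of the center-only model was 4.7%, 3.6% and 2.8%, at or below the nominal 5% throughout.

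**Adding center differences.** A second simulation (6,000 runs per scenario) let the centers differ as well. Power is given as unadjusted / center / center plus T1D:

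- Centers 0, 0.5, 1 and T1D +0.5: 83.5 / 83.8 / 84.0%.
- Centers 0, 1, 2 and T1D +1: 84.3 / 85.9 / 86.3%.
- Centers 0, 1.5, 3 and T1D +2: 85.8 / 89.1 / 91.3%.

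Using neither factor costs 0.5, 2.0 and 5.5 points against full adjustment; omitting T1D alone costs 0.2, 0.4 and 2.2.

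**Other splits.** If all 34 Spanish participants have T1D, center and center plus T1D are the same model and nothing is lost by omitting T1D. For a fixed gap, the 17/17 split gives the largest within-Spain variance, so it is the least favorable case for the center-only model.

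**The case against.** The strongest reply is that the loss is small and depends on assumptions. Gaps of 2 and 3 points are about 1.0 and 1.4 SD (2/2.07 and 3/2.07), larger than the 1.3-unit effect the trial seeks. Nothing in the article supports gaps of that size on a score that rates each person's own goal. In every scenario above, center-only power at 88 before dropout exceeds 80%, so the loss is a gain forgone against a better model. The planned center regression already recovers the center differences. All of this stands and sets the size of the point.

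Two stronger readings do not stand. A reader might infer that the omission makes the error bars wrong in a harmful direction. It does not: with stratified allocation the intervals err on the wide side, and only if the strata matter.

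A reader might also infer three competing P values with none designated. The order of the text, the word also before the regression, and a sample size built on a two-sample t test make the regression read as supplementary. What stays open is t versus Mann-Whitney, a rule that an article may leave to the analysis plan.

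For the baseline-adjusted models, the baseline value may already absorb stable stratum differences. Center is constant for the blood and physical measures taken only in Spain, and T1D status is constant for HbA1c and sensor outcomes. No loss has been calculated for any of these.

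**Conclusion.** The mismatch is real: two factors in the randomization, none in the first-listed test, one in the added regression. It is a modest efficiency flaw with no bias and no excess of false positives. Under the assumed 17/17 Spanish split, 88 participants and total SD 2.07, omitting T1D from the center-adjusted model costs up to about half a power point for gaps up to 1 point, about 2 points at a 2-point gap and about 5 at a 3-point gap. Using neither factor costs up to 5.5 points in the most extreme scenario examined. With no stratum differences the cost is zero. That Spain enrolled both populations is an inference: stratifying by T1D as well as center would otherwise be redundant.

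**What to change.** State one primary analysis: linear regression of the Likert score on arm plus the randomization strata (center and T1D status, at most four strata), reporting the adjusted mean difference with its 95% CI. Keep the t test and the Mann-Whitney test as sensitivity analyses. If T1D status is left out, say why.

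Add the same stratum terms to the baseline-adjusted models for outcomes measured in all participants, and T1D status to the models for Spain-only outcomes measured in both populations.

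The cost is one or two sentences and one degree of freedom beyond center adjustment; no new data are needed. The article says that the analysts are blinded and that analysis is under way, so the change should be dated and fixed before they are unblinded.

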### Power and Sample Size

The sample size was calculated for the primary outcome (Likert scale from 1 to 10 with a target defined by the participant). A population of people with T1D was used as the reference population, based on a previous study [38,49]. The common SD in the intervention and control groups is assumed to be 2.07 [38]. With a significance level of 0.05 and a power of 0.8 in a 2-sided 2-sample *t* test (2-tailed), 47 subjects are necessary in both groups to detect a statistically significant difference greater than or equal to 1.3 units. Allowing for a potential loss to follow-up of 10%, we estimated a total required sample size of 52 participants in each group. Participants with T1D are only recruited in Spain. All 3 centers aimed to recruit an equal number of participants, that is, 36 participants each (aiming at a total of 108).

The analyses will primarily be performed on the total sample for common outcomes. Regarding the group of participants with T1D, as the study lacks the power to detect clinically relevant changes in T1D-specific clinical outcomes, no definitive conclusions will be drawn from these results. Instead, the results will inform sample size estimation and the design of a subsequent trial targeting the T1D population specifically.

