## Results

The clinical trial began in January 2025. A total of 88 participants were recruited from 3 centers: 34 from Spain, 34 from Norway, and 20 from Romania (Figure 3). Participants were randomized at a ratio of 1:1 to either the intervention or control group (42 participants in the intervention group and 46 in the control group). Each participant was observed for up to 12 weeks in total, with the follow-up period ending in June 2025. The data are currently being analyzed and are expected to be published in 2026.

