## Discussion

### Anticipated Findings

The RCT we describe aims to assess the short-term effectiveness of the WARIFA app in promoting users’ healthy behaviors and self-management of T1D. Our hypothesis is that dynamic, personalized recommendations can achieve self-defined objectives and healthy behavior changes to a larger extent than general recommendations for all users.

Other mHealth apps have been used for behavior change and disease management in patients with hypertension and obesity [50,51], although they do not provide estimates of the risk of NCDs.

The main strengths of this trial are that it is conducted in 3 European countries and includes a fairly large and heterogeneous sample size, which should support the applicability of the results. Furthermore, the use of a low-intervention app and a physical activity monitor as control, as well as the double-blind nature of the trial, reduces the risk of bias. The WARIFA app can provide personalized risk estimations for the major NCDs over the next 10 years, as well as identifying the habits to change and the most effective way to do so for each individual. This is in contrast to the generic messages typically used in community-based prevention. The app is able to deliver these personalized messages to participants’ devices to encourage adherence. A key strength of the WARIFA project is its rigorous commitment to data protection, robust algorithmic support, user autonomy, and full transparency in AI‑driven recommendations.

We also acknowledge some limitations in the design of the trial. Although we believe that the number of participants is appropriate for an initial evaluation of the WARIFA app, it may not be sufficient to assess many of the secondary outcomes addressed, especially in T1D. Another limitation is that the biomedical outcomes (anthropometry and blood tests) are performed at one of the centers only, and these data will not be available for all participants. Restrictions also include the fact that the WARIFA app is only compatible with Android mobile phones, as well as certain activity devices and glucose sensors. mHealth apps have boomed in recent years as a tool that is free, voluntary, and easy to obtain. However, many users uninstall the app shortly after installation [52].

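### The stated 47 per group does not follow from the stated inputs: SD 2.07, difference 1.3 and 80% power give 41 per group, and 47 gives about 85% power

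*Protocol article*

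**What the plan says.** The Power and Sample Size section of the protocol article bases the calculation on the primary outcome, the self-rated goal achievement score from 1 to 10. It gives the variability ("The common SD in the intervention and control groups is assumed to be 2.07"), the test and error rates ("With a significance level of 0.05 and a power of 0.8 in a 2-sided 2-sample" t test) and the result ("47 subjects are necessary in both groups to detect a statistically significant difference greater than or equal to 1.3 units"). After a 10% allowance for loss to follow-up, "we estimated a total required sample size of 52 participants in each group", which is 104 in total. The recruitment aim was 36 at each of three centers, 108 in all. The Randomization and Blinding section gives 1:1 allocation.

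The Statistical Analysis section compares the groups by a t test or a Mann-Whitney test. The Results section reports enrolment: "A total of 88 participants were recruited from 3 centers", with 42 in the intervention group and 46 in the control group.

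**The concern.** All the inputs and the result stand in one paragraph, so the result can be checked directly, and it does not come out. The gap is 6 per group. That is too large for rounding, or for the choice between a normal approximation and an exact t calculation, which differ here by one participant.

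The power statement matters because it frames how a null primary result will be read. Someone who compares the stated requirement of 104 with the 88 enrolled sees a shortfall of 16 (16/104 = 15%) and may conclude that the trial missed its 80% target by a wide margin. The stated SD and difference point elsewhere: the requirement they imply is lower, and the enrolled number is close to it. As printed, the paragraph does not let the reader tell which account is right.

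**Working it through.** **Inputs**, from Power and Sample Size unless noted: two-sided alpha 0.05; power 0.80; SD 2.07; difference 1.3; loss 10%; allocation 1:1 (Randomization and Blinding); enrolled 42 and 46 (Results). The standardized difference is d = 1.3/2.07 = 0.628.

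**Attempt to reproduce 47**

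- Normal approximation: n per group = 2 × (1.960 + 0.842)² × (2.07/1.3)² = 2 × 7.85 × 2.535 = 39.8, so 40.
- Noncentral t, the exact form for the named test: solving for 80% power gives 40.78, so 41.
- The stated 47 is not reproduced.

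**What 47 corresponds to** (noncentral t)

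| Question | Result |
|---|---|
| Power at 41 per group | 80.2% |
| Power at 47 per group | 85.4% |
| n per group for 85% power | 46.51, so 47 |
| n per group for 90% power | 54.26, so 55 |
| Difference giving 47 at 80% power, SD 2.07 | 1.21 |
| SD giving 47 at 80% power, difference 1.3 | 2.23 |

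**Other routes tried**

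- A one-sided test at 0.05 gives 33, 38 and 45 per group for 80%, 85% and 90% power. None is 47.
- Mann-Whitney allowance by relative efficiency: 40.78/0.955 = 42.7, so 43; 40.78/0.864 = 47.2, so 48.
- Mann-Whitney allowance as a flat 15%: 40.78 × 1.15 = 46.9, so 47.

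Two simple routes therefore land on 47: a power of 85%, or a flat 15% allowance on the 80% figure. The paragraph mentions neither.

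**Allowance for loss**

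- On 41: 41/0.9 = 45.6, so 46 per group and 92 in total.
- On 47: 47 × 1.1 = 51.7, so 52, which is the stated figure.

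**What the enrolled number gives on the stated SD and difference** (noncentral t, two-sided 0.05)

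| Analysed | Power at 1.3 | Difference detectable at 80% power |
|---|---|---|
| 42 and 46 (no loss) | 82.9% | 1.25 |
| 37.8 and 41.4 (10% loss in each group) | 78.7% | 1.32 |

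Against the requirement recomputed from the stated inputs, 88 is 4 below 92. Against the printed requirement, it is 16 below 104.

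**The case against.** The strongest reply is that the discrepancy does no harm. Forty-seven is more than the stated inputs need, recruitment is over, and neither the endpoint nor the analysis changes. This stands, and it limits the weight of the point: on the stated inputs the error never led to too small a target.

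A second reply is that every stated input may be right. The analysis section allows a Mann-Whitney test, and a flat 15% allowance for it gives 47. This is a fair possibility, but it does not rescue the sentence, which attributes 47 to a t test and mentions no allowance.

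The same possibility rules out a stronger reading that a reader might reach, that the SD, the difference or the power must be wrong. An SD of 2.23 or a difference of 1.21 would produce 47, but nothing in the document points to either, and an unstated allowance would leave all three inputs intact.

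Three further inferences are not supported:

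- **That 52 should be 53.** Dividing 47 by 0.9 gives 52.2, but multiplying by 1.1 gives 51.7, so 52 follows from an ordinary convention. The recruitment aim of 108 is 54 per group, and 54 × 0.9 = 48.6 still exceeds 47.
- **That it is an error not to restate power for 88.** A sample size section records the planning calculation, and the article openly reports both the enrolment and the split.
- **That the Discussion misleads where it says the trial "includes a fairly large and heterogeneous sample size".** This is a matter of wording. The same section limits its claim to an initial evaluation and says the number may not suffice for many secondary outcomes.

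**Conclusion.** The point holds as a mismatch between the printed sample size and its printed inputs. With a two-sided two-sample t test at 0.05, SD 2.07 and a difference of 1.3, 80% power needs 41 per group. The 47 printed is 6 higher and gives 85.4%. The document does not show whether the power was misstated, another SD or difference was used, or an allowance was left out.

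The direction is conservative. On the stated inputs, the enrolled 42 and 46 give about 83% power with no loss and about 79% with 10% loss in each group, so the trial sits close to its 80% goal despite falling short of 104. These figures assume that the stated SD and difference are the intended ones, that loss is equal in the two groups, and that the comparison is the unadjusted t test. They do not address whether an SD taken from a type 1 diabetes population carries over to the general population participants; that is a separate question, and the article gives no other SD. The correction is minor to moderate.

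**What to change.** Correct the sentence in Power and Sample Size in whichever of these ways matches the calculation actually made:

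1. State 41 per group for 80% power, which is 46 per group (92 in total) after 10% loss.
2. Keep 47 per group and state that it is for 85% power.
3. Keep 47 at 80% power and state the SD, the difference or the allowance (for example, for a nonparametric test) that produced it.

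In the same revision it would be useful to add one sentence on the enrolled number. Under option 1 or 2, or if only an allowance is disclosed, it can say that with SD 2.07 the 42 and 46 randomised give about 83% power at 1.3 points with no loss (detectable difference 1.25) and about 79% after 10% loss (1.32). If another SD or difference is disclosed, these figures must be recomputed from it. Under the allowance option they apply to the t test without the allowance, and the sentence should say so.

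The cost is a text correction. No participants, data or analyses change. The article says the data are still being analysed, so the correction can be made before results are published.
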